**Assessments:**						
Demographics		X				
Purpose-designed 3-item questionnaire assessing exposure to suicide and suicide prevention training		X				
Suicidal Ideation Attributes Scale (SIDAS)		X	X		X	X
Single item measuring current suicidal ideation		X	X		X	X
Youth Risk Behaviour Survey (YRBS)—suicide items		X	X		X	X
Patient Health Questionnaire-9 (PHQ-9)		X	X		X	X
Distress Questionnaire-5 (DQ-5)		X				
Hopelessness Scale for Children (HSC)		X	X		X	X
Negative Problem Orientation Questionnaire (NPOQ)		X	X		X	X
Resource Use Questionnaire (RUQ), adapted from the Young Mind Matters Service Use questionnaire (BRIEF VERSION)		X				
Resource Use Questionnaire (RUQ), adapted from the Young Mind Matters Service Use questionnaire (FULL VERSION)			X		X	X
Purpose-designed questionnaire asking about previous help-seeking behaviour and future help-seeking intentions from family, friends and other “informal” sources of help		X	X		X	X
4-item measure of attitudes towards help-seeking from adults at school, derived from the previous US Sources of Strength (SOS) trial and currently being used in the Australian SOS trials		X	X		X	X
4-item measure assessing attitudes towards overcoming secrecy barriers, derived from the previous US Sources of Strength (SOS) trial and currently being used in the Australian SOS trials		X	X		X	X
Willingness to Intervene Against Suicide Questionnaire (WIS)		X	X		X	X
Stigma of Suicide Scale (SOSS)—short form		X	X		X	X
Literacy of Suicide Scale (LOSS)—short form		X	X		X	X
Child Health Utilities Index 9 Dimension (CHU9D)		X	X		X	X
Purpose-designed 7-item questionnaire assessing acceptability of safeTALK training			X			
Purpose-designed 11-item questionnaire assessing acceptability of the Reframe IT intervention (or of not receiving it)					X	
Two items from the Patient Health Questionnaire-4 (PHQ-4), measuring anxiety		X				
Purpose-designed 11-item scale measuring experimentally induced distress, adapted from Yeater, Miller, Rinehart and Nason (2012)						X

***Note. Informed consent for Reframe IT participation and evaluation will be collected from eligible participants between Times 1 and 2, prior to randomisation and commencement of the Reframe IT intervention

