Assessments will take the form of self-report questionnaires, and where possible will be collected using a computer or tablet employing REDCap (Research Electronic Data Capture), a secure, web-based data capture application hosted at The University of Melbourne [43, 44]. Where questionnaires are completed on paper, these will be later entered into REDCap by a member of the research team. Assessments will be completed at school in class groups, facilitated by a researcher, and supervised by a school staff member.

The REDCap system will automatically flag any participants who score between 1 and 20 on the SIDAS, as 1 is the established cut-off score indicating any level of suicidal ideation in the past month [45]. In the case that participants are required to complete paper versions of the questionnaire, they will be asked to include their full name on a separate detachable cover sheet. After the survey is completed, research staff will manually check their scores on the SIDAS instrument.

Within five school days of the baseline assessment, the research team will contact students who score between 1 and 20 on the SIDAS and conduct a brief semi-structured interview to determine eligibility for Component 2. Eligible students will be invited to participate and those who are interested will be given a consent form to be signed. They will then be randomised to either the intervention (Reframe IT) or control group (see below). A member of the research team will inform the relevant school staff member of the outcome of the randomisation.

Two weeks after the baseline assessment, safeTALK workshops will be delivered to all participating students. Immediately following the workshop, students will complete the T2 questionnaire. Students randomised to receive the Reframe IT intervention will complete the eight modules in the 10 weeks between T2 and T3 (i.e. approximately one module per week plus two additional weeks to allow for disruptions such as school holidays). Both T3 and T4 assessments will occur during class time; T4 will occur 12 weeks after T3. Researchers will be present at T3 and T4 assessment points if deemed appropriate by the research team and/or if requested by the school (e.g. they perceive a need for additional administrative support). No biological samples will be collected.

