### Outcomes and measures

#### Primary outcome

The primary outcome for this study is change in past 4-week suicidal ideation at T3 and T4 when compared to T2, assessed via the SIDAS [45]. The SIDAS is designed to screen individuals in the community for presence of suicidal thoughts and assess the severity of these thoughts. It comprises five items, each targeting an attribute of suicidal thoughts: frequency, controllability, closeness to attempt, level of distress associated with the thoughts and impact on daily functioning. Responses are measured on a 10-point scale. Total SIDAS scores are calculated as the sum of the five items, with controllability reverse scored (10 = 0, 9 = 1,…, 0 = 10), with total scale scores ranging from 0 to 50. Items are coded so that a higher total score reflects more severe suicidal thoughts.

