### Sample size and power calculation

The critical power calculation for this study relates to Component 2 (RCT of Reframe IT). The primary outcome variable for Reframe IT is reduced suicidal ideation, measured by the SIDAS, at 24 weeks (T4), in comparison to SIDAS scores at Time 2.

The Suicidal Ideation Questionnaire (SIQ) [61, 62] was used in the Reframe IT pilot study [33]. The SIQ and SIDAS are both continuous self-report measures of the frequency of cognitions related to suicide within the past month, with higher scores corresponding to more frequent and severe suicidal ideation. The range of the SIDAS is 0–50 and the range of the SIQ is 0–180. A SIDAS score of 1 or more indicates “risk for suicide”, whereas a SIQ score of 41 or more indicates “need for further evaluation of psychopathology”. As the SIQ licence is too expensive to use on a large scale, the SIDAS is being used in its place. In the absence of pilot data for the SIDAS, the power calculation is based on the SIQ. This can be reasonably justified given the similarities between the measures and their cut-offs and has been calculated in consultation with the study statistician.

In the Reframe IT pilot study, there were three time points of data collection (corresponding to T2, T3, and T4 as labelled in the current study). The mean reduction in SIQ between T1 and T3 (i.e. corresponding to T2 and T4 in the present study) for the pilot control group was 61.6 points (SD = 42.3) and for the pilot intervention group this was 47.1 points (SD = 41.6). The difference between these two reductions was 14.5 points. We also observed an intra-class correlation of 0.023 within schools, which gives a design effect of 1.1. Using these data, and making the conservative assumption that there is no correlation between SIQ scores within individuals over time, a 5% significance level and 80% power means that a sample size of 134 per arm (268 in total) is required.

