### Randomisation and treatment allocation

Students who consent to participate in Component 2 will be randomised to the intervention group (Reframe IT plus TAU) or to the control group (TAU only) using block randomisation with varying block sizes and stratified by school. The allocation ratio will be 1:1. The randomisation schedule is computer generated by independent Information Technology (IT) personnel with guidance from the study statistician. The schedule will then be implemented by a member of the study team (other than the statistician) into the REDCap database management software for allocating treatments to individual students.

A member of the study team will inform school wellbeing staff of the outcome of randomisation, and they will then inform students. With the exception of the study statistician, study team members are not blind to the treatment allocations. The study statistician will not have access to the randomisation component of the database and will not be told about the treatment allocations, and will therefore remain blinded. As the study statistician will not be involved in any aspect of this study operations other than data analysis, there are no circumstances we could foresee under which the study statistician would be required to be unblinded.

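### The primary outcome is change from T2, but as sequenced students are generally randomised, and may know their arm, before they complete T2

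*Protocol article*

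**What the plan says.** The Primary outcome section defines the endpoint as "change in past 4-week suicidal ideation at T3 and T4 when compared to T2, assessed via the SIDAS". The Sample size and power calculation section repeats the reference: "at 24 weeks (T4), in comparison to SIDAS scores at Time 2". In the Secondary outcomes section, PHQ-9, HSC and NPOQ are also measured as change from T2.

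The Procedure section gives the order of events. Students complete T1. Those scoring 1 to 20 on the SIDAS are interviewed within five school days. Eligible and interested students receive a consent form, and "They will then be randomised to either the intervention (Reframe IT) or control group (see below". A study team member tells the school the result. The workshop follows two weeks after T1, and "Immediately following the workshop, students will complete the T2 questionnaire". The note to Table 1 places consent for Reframe IT "between Times 1 and 2, prior to randomisation and commencement of the Reframe IT intervention", and the Recruitment section allows two weeks from baseline for that consent.

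On disclosure, the Randomisation and treatment allocation section says: "A member of the study team will inform school wellbeing staff of the outcome of randomisation, and they will then inform students". It gives no date for this. Apart from the statistician, the study team is not blinded, and all assessments are self-reported.

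**The concern.** Randomisation makes the arms comparable only on what is measured before the allocation can act. Here the zero point of the primary change score is a questionnaire that a student may fill in already knowing the arm. Disappointment in the control arm, or relief in the Reframe IT arm, could move the answers. So could extra support arranged before T2 by wellbeing staff who know the allocation. The change score subtracts any such difference from the treatment effect.

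The direction is not fixed. Higher control scores at T2 caused by disappointment would make Reframe IT look worse, because controls would start from a raised value. Extra early support for controls would do the reverse. A blinded statistician cannot remove either effect while T2 remains the reference.

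**Working it through.** **Sequence.** Taking the steps in the order in which the Procedure section gives them:

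1. T1, with SIDAS collected from everyone.
2. Interview where required, within five school days.
3. Consent, between T1 and T2.
4. Randomisation; the school is told, and staff then tell students.
5. safeTALK two weeks after T1, then T2 immediately.
6. Reframe IT modules in the 10 weeks between T2 and T3.

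T2 therefore precedes the modules but generally follows randomisation.

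**What the contrast estimates.** Let D1, D2 and D4 be the expected SIDAS differences (Reframe IT minus control) at T1, T2 and T4. The effect of being allocated to Reframe IT is D4. The change contrast is D4 − D2.

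- If nobody acts on or knows the allocation before T2, D2 = 0 and the contrast equals D4.
- If knowing the allocation shifts T2 by d, the contrast is D4 − d, an error of exactly d in size.
- T1 always precedes randomisation, so D1 = 0 in expectation.

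**Recall periods.** SIDAS covers four weeks and T2 falls two weeks after T1, so at least 2/4 = half of the T2 recall period predates T1, and more predates any allocation. PHQ-9 covers two weeks and HSC one week, so these are more exposed.

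**Illustration of scale (assumed shifts, not estimates).** Inputs from the Sample size section are on the SIQ, the pilot's scale: difference 14.5, SDs 42.3 and 41.6, 134 per arm, 5% significance (two-sided assumed) and 80% power.

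- Pooled SD = √((42.3² + 41.6²)/2) = 41.95.
- n = 2 × (41.95 × (1.960 + 0.842)/14.5)² = 131.4, so 132 per arm. Using 42.3 gives 133.6, so 134. The stated 134 is thus matched without the quoted design effect of 1.1. That is a separate matter, and the design effect is left out below.
- Standard error = 41.95 × √(2/134) = 5.13. Power with no shift = Φ(14.5/5.13 − 1.96) = 81%.
- With shift d: type I error = Φ(−1.96 + d/5.13) + Φ(−1.96 − d/5.13). Power when the shift works against a true 14.5-point effect = Φ((14.5 − d)/5.13 − 1.96).

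| Assumed T2 shift (SIQ points) | Share of 14.5 | Type I error | Power if it masks the effect |
|---|---|---|---|
| 0 | 0% | 5.0% | 81% |
| 1 | 7% | 5.4% | 75% |
| 2 | 14% | 6.8% | 68% |
| 3 | 21% | 9.0% | 61% |
| 5 | 34% | 16.4% | 46% |

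**The case against.** **The timing is not dated.** No section fixes randomisation or disclosure relative to T2. Consent may come as late as two weeks after baseline, which is about T2 itself, and a missed baseline may be completed any time before T2. Some students could therefore be randomised at or after T2. This stands, and it limits the point to what can happen under the stated sequence. The article is condensed, and release of the allocation is an operational step. Yet the article does not merely omit it: the order it prints puts randomisation first.

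**T2 has a rationale.** It is the last measurement before the modules, it follows the workshop that all participants are offered, and it matches the pilot's first time point. This explains the choice and justifies keeping change from T2 as a supporting analysis. It does not require randomisation before T2.

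**The mechanism may be weak.** The four-week recall dampens a shift, both arms receive usual care, and any SIDAS score of 1 or more triggers follow-up in either arm. This also stands; it lowers the likely size without making it zero.

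**Stronger readings that the documents do not support.**

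- A reader might infer that a missing T2 breaks the intention-to-treat analysis. The Statistical analyses section specifies a linear mixed model and considers multiple imputation, and either can retain such students. All students are also asked for later questionnaires whether or not they completed safeTALK.
- A reader might rescale 14.5 SIQ points to 14.5/180 × 50 = 4.0 SIDAS points, assume a shift of 0.5 to 1 point, and conclude that the bias is 12% to 25%. The shift has no source. The article's own cut-offs (41 of 180 = 23%; 1 of 50 = 2%) show that the two scales do not map linearly.
- T2 is not contaminated by Reframe IT itself, because the modules start later.

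**Conclusion.** The point holds as a risk built into the stated sequence, not as a demonstrated bias. Following the Procedure section as written, the reference value for the primary outcome and for three secondary outcomes can be an unblinded self-report taken after randomisation. Any difference at T2 caused by knowing the allocation enters the contrast in full. Its size and direction are unknown, and with no shift there is no bias. The table above only shows how sensitive the planned comparison would be. It rests on assumed shifts, the SIQ planning figures, a two-sided test and no design effect.

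**What to change.** State in the Procedure and the Randomisation and treatment allocation sections that students are randomised only after the T2 assessment session, whether or not the individual student attended it. At the least, state that the allocation is released to school staff and students only then. Randomising after T2 is the cleaner option, because unblinded researchers facilitate the assessments. The modules run between T2 and T3, so they are not delayed.

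If any student was randomised or informed before T2, use the T1 SIDAS as the baseline covariate for all randomised students in the primary model. Do not mix T1 and T2 baselines: that would combine values from before and after the workshop in one model. Eligibility rests on the T1 SIDAS, so every eligible student has it. Keep change from T2 as a supporting analysis. The T2-referenced secondary outcomes can be treated in the same way, since PHQ-9, HSC and NPOQ are also collected at T1.

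The cost is small. Staff learn the allocation some days later, closer to the first module. A T1 baseline precedes the shared workshop and may correlate slightly less with T4, with some loss of precision.

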### Interventions

#### safeTALK

safeTALK, developed by LivingWorks Education [46], is a suicide alertness training workshop, suitable for anyone over the age of 15. It comprises a single 3.5-h face-to-face workshop, designed to help participants understand suicide warning signs in themselves and others, gain knowledge about appropriate sources of help for suicidal feelings, apply basic “TALK” steps (Tell, Ask, Listen, and KeepSafe), and feel better able to connect a person at risk of suicide with appropriate help. safeTALK workshops will be delivered by trained Lifeline Australia facilitators to classroom-sized groups of students (maximum of 30 students per session). A researcher will attend each workshop.

#### Screening for risk

The screening will take the form of self-report measures embedded into the questionnaires at each time point. Students who report suicidal ideation within the past 4 weeks (SIDAS score of 1 or higher) or any level of current suicidal ideation (single multiple-choice item) will be contacted by a member of the school wellbeing team or the research team, who will assess risk and refer them to appropriate support.

#### Reframe IT

The Reframe IT intervention has been described elsewhere [33–35]. In brief, it comprises eight 20-min self-guided CBT modules. It follows the stories of two young people who make video diaries about their day-to-day life and their experience of feeling suicidal. An adult “host” character guides the user through the module and activities. Each module contains two “activities” based on standard CBT exercises. Users progress sequentially through the content, with modules automatically unlocked when the preceding module is complete. There is also a message board through which the participant can communicate with a moderator, a mood diary function, and a series of factsheets and information on local and national helplines and services.

#### Control intervention

Participants randomised to the control group will receive TAU (e.g. from the school counsellor or external mental health services). The specific nature of TAU will be determined by the wellbeing team at each school. Although this may result in variability in treatment type between sites, the use of TAU as a comparator will facilitate an evaluation of whether receipt of the Reframe IT intervention is associated with improvement over current practice [47]. The wellbeing team at each school will be asked to record what TAU comprised for each student.

#### Strategies to improve adherence to intervention protocols

The safeTALK intervention will be delivered by qualified Lifeline facilitators, following a standardised format. The study team will provide on-boarding training to school wellbeing staff regarding the use of the Reframe IT online platform, and additional training sessions will be offered as required. Each participating school will be provided with a study manual.

#### Procedures for monitoring compliance with the intervention

To monitor compliance with safeTALK, a question will be included in the T2 questionnaire asking if participants were present for the entire safeTALK workshop. If participants respond “no”, they will be asked to indicate how much of the session they were present for. A researcher will be present for the delivery of safeTALK and will keep a record of any students who leave the session prematurely, including the amount of time and number of workshop modules the participant was present for.

Compliance with the screening intervention will be determined by assessing whether or not participants complete the suicide risk questions.

Participants’ use of Reframe IT (including a number of log-ins, number of modules completed, and responses to activities) will be automatically recorded by the system. At the conclusion of the study, usage statistics will be evaluated.

#### Concomitant medication and therapies

The nature of the study population is such that some participants may already be taking prescribed medications. There are no restrictions to participation based on concomitant medication or therapies.

### Outcomes and measures

#### Primary outcome

The primary outcome for this study is change in past 4-week suicidal ideation at T3 and T4 when compared to T2, assessed via the SIDAS [45]. The SIDAS is designed to screen individuals in the community for presence of suicidal thoughts and assess the severity of these thoughts. It comprises five items, each targeting an attribute of suicidal thoughts: frequency, controllability, closeness to attempt, level of distress associated with the thoughts and impact on daily functioning. Responses are measured on a 10-point scale. Total SIDAS scores are calculated as the sum of the five items, with controllability reverse scored (10 = 0, 9 = 1,…, 0 = 10), with total scale scores ranging from 0 to 50. Items are coded so that a higher total score reflects more severe suicidal thoughts.

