## Methods

### Study design

The present study will adopt two methodological approaches: Component 1 will employ a single-group, pre-test/post-test case series; Component 2 is a parallel superiority randomised controlled design, where the intervention condition (Reframe IT plus treatment as usual; TAU) is compared to TAU. Component 2 will be conducted and reported according to the Consolidated Standards of Reporting Trials (CONSORT) statement [36].

The study was designed to be conducted over a 5-year period (2019–2023), with a 3-year intervention phase. There has, however, been a 1-year suspension due to the COVID-19 pandemic during 2020, meaning that the study will continue into 2024.

The study is registered with the Australian New Zealand Clinical Trials Registry (ID: ACTRN12621000770864). This is the primary registry of the WHO ICTRP network. It includes all items from the WHO Trial Registration data set, available at https://www.anzctr.org.au/Trial/Registration/TrialReview.aspx?id=381921&isClinicalTrial=False. It received ethical approval from the University of Melbourne Human Research Ethics Committee (HREC; ID 1852317) and the Department of Education Victoria Research Ethics Committee (ID 2019_003951) [see Additional files 2 and 3].

This protocol is reported in line with the Standard Protocol Items: Recommendations for Interventional Trials (SPIRIT) 2013 statement [37, 38] [see Additional file 4 for checklist].

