### Statistical analyses

#### Component 1

For each continuous outcome, changes over time will be assessed using linear mixed effects modelling with school included as a random factor. This analysis will examine whether there is a trend over time and whether the trend is linear or non-linear. Change in current suicidal ideation between T1 and T2 will be assessed using the McNemar–Bowker symmetry test for nominal data.

#### Component 2

Descriptive statistics will be used to compare participant characteristics between the study arms, and to assess for any imbalance.

The analysis will adopt the intention-to-treat approach, which is to include in the analysis all participants who have been randomised and regard each participant as belonging to the randomised group concerned irrespective of protocol adherence. Difference in change in the primary outcome of SIDAS score between the treatment groups will be examined using linear mixed effects modelling with the treatment group as a fixed factor and school included as a random factor. Secondary outcome measures will be similarly analysed. As a secondary analysis, compliance (as measured by the number of modules completed) and other potential covariates (e.g. gender) will be accounted for.

If the amount of missing data is non-trivial, multiple imputation will be considered to handle the missing data.

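### The primary outcome of the Reframe IT trial is set at T3 and T4 in one section and at T4 alone in another, and the analysis section does not say which contrast decides

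*Protocol article*

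**What the plan says.** Three sections of the protocol article bear on this.

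- **Primary outcome:** "The primary outcome for this study is change in past 4-week suicidal ideation at T3 and T4 when compared to T2", measured by the SIDAS. This names two follow-up times.
- **Sample size and power calculation:** here the primary variable of the randomised component is given as "reduced suicidal ideation, measured by the SIDAS, at 24 weeks (T4), in comparison to SIDAS scores at Time 2". This names one follow-up time. The calculation uses the pilot change corresponding to T2 to T4: "The difference between these two reductions was 14.5 points". It concludes that "a 5% significance level and 80% power means that a sample size of 134 per arm (268 in total) is required".
- **Statistical analyses, Component 2:** "Difference in change in the primary outcome of SIDAS score between the treatment groups will be examined using linear mixed effects modelling", with treatment group fixed and school random. No time point, joint test or averaged contrast is named.

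The abstract and the hypotheses speak only of suicidal ideation being changed or reduced, without a time point, so they do not settle the matter. Component 2 is a "parallel superiority randomised controlled design", so one comparison has to carry the superiority claim.

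**The concern.** By the Procedure section, T3 falls at the end of the Reframe IT period and T4 comes 12 weeks later. The two times answer different questions: effect at the end of treatment, and effect that lasts. A benefit at one and not at the other is quite possible. On the present wording, a result at T3 only could be reported as a positive primary outcome under one section and as a failed one under another.

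Two things are at stake. The first is the error rate, if both times are tested and either may carry the claim. The second is the power, if both are needed, because 134 per arm was worked out for one contrast. The Randomisation section says that the study team, apart from the statistician, is not blinded. That is a further reason to have the decisive contrast fixed in the protocol before results are seen.

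**Working it through.** **Inputs from the Sample size section.** Difference 14.5 SIQ points; SD of change 42.3 (control) and 41.6 (intervention); significance level 5%; power 80%; 134 per arm. Sidedness is not stated, and two-sided is assumed here.

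**Input not in the document.** The correlation r between the T3 and T4 test statistics. It is assumed, and the range 0 to 0.9 is shown.

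**Step 1: reproduce the plan's figure.** For one comparison of two means,

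n per arm = 2 × [SD × (1.960 + 0.8416) / 14.5]²

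- SD 42.3: 2 × (42.3 × 2.8016 / 14.5)² = 133.6, so 134. This matches.
- Pooled SD √[(42.3² + 41.6²)/2] = 41.95: 131.4, so 132.

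A one-sided 5% level gives 102 to 106, which does not match. So 134 per arm is the size for one two-sided test of one contrast, T2 to T4, at the full 5%. Nothing in it provides for a second primary comparison. (The match leaves out the stated design effect of 1.1. That is a separate matter and is not used below.)

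**Step 2: T4 alone is primary.** There is one test at 5%. With pooled SD 41.95, the expected test statistic is 14.5 / [41.95 × √(2/134)] = 2.829, and power is Φ(2.829 − 1.960) = 80.8%. Nothing changes.

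**Step 3: T3 and T4 tested separately at 5%, either sufficing.** Familywise error = 1 − P(|Z₁| < 1.96 and |Z₂| < 1.96), with (Z₁, Z₂) bivariate normal.

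| r | Familywise error |
|---|---|
| 0 | 9.75% (= 1 − 0.95²) |
| 0.5 | 9.1% |
| 0.7 | 8.3% |
| 0.9 | 7.0% |

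**Step 4: both required.** Power = P(both statistics exceed 1.96). This also assumes the same effect at T3 as at T4; the document gives no T3 effect.

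| r | Each at exactly 80% | Each at 80.8% (134 per arm, pooled SD) |
|---|---|---|
| 0 | 64% (= 0.80²) | 65% |
| 0.5 | 69% | 70% |
| 0.7 | 71% | 72% |
| 0.9 | 75% | 76% |

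**Step 5: both kept, with the 5% split equally.** At 0.025 each, the two-sided critical value is 2.241. Power per time point at 134 per arm is Φ(2.829 − 2.241) = 72%. For 80% at each time point, n = 2 × [41.95 × (2.241 + 0.8416) / 14.5]² = 159.1, so 160 per arm (320 in total).

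**The case against.** A reader might infer that the trial must have either an inflated type I error or less power than stated. The documents do not support that.

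- The Sample size section is specific to the randomised component and says outright that T4 is primary. If it governs, neither harm arises from this issue.
- The Primary outcome wording can be read as a measurement schedule. The Secondary outcomes section uses the same T3-and-T4-versus-T2 formula for the PHQ-9, HSC and NPOQ.
- No section describes two separate tests at 5%, or a rule that both must succeed. The only significance level is the one attached to the T2-to-T4 calculation.
- The mixed model could test one joint or averaged contrast, which would hold the error at 5%. Its power cannot be computed from the document.
- Rules on contrasts and multiplicity commonly sit in a statistical analysis plan, and that plan is not shown. It therefore cannot be said that the choice of time point is in fact open.

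All of this stands, and it makes the consequence conditional. It does not remove the conflict. Two explicit statements in the same article define the primary outcome differently. That is not a detail left to another document, and whatever an analysis plan says, one of the two sections needs correcting.

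**Conclusion.** The inconsistency is established from the text: two time points in one section, one in another, and no decisive contrast named in the analysis section. The plan's 134 per arm belongs to the T2-to-T4 contrast alone.

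The numerical consequence is conditional:

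- T4 alone governs: no effect on error or power.
- Both tested separately at 5%, either sufficing: familywise error about 7% to 10%.
- Both required, each with about 80% power: overall power about 64% to 76%.

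The last two ranges rest on an assumed correlation of 0 to 0.9 between the test statistics. The power range also rests on an assumed T3 effect as large as that at T4. They show what is at risk if the Primary outcome section were followed in those ways; they are not properties of the trial as planned. The point still needs correcting, because the confirmatory claim cannot be judged until it is clear which comparison is primary.

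**What to change.** In the Primary outcome section, name the change in SIDAS from T2 to T4 (24 weeks) as the single primary outcome, and list the change from T2 to T3 as secondary. In the Statistical analyses section for Component 2, name the between-group difference in T2-to-T4 change as the decisive contrast from the mixed model. This agrees with the existing sample size. It costs a wording amendment, notified to the registry and the journal as the protocol already provides, with no added data or participants.

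If the sponsor prefers to keep both time points as primary, the plan should state one joint test or an alpha rule and restate the power for it. With an equal split and 80% power per time point, that would be about 160 per arm on the plan's own inputs, before design effect and dropout. Either way, the change should be made before outcome data are seen by treatment group.
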